## Abstract

**Background:**

Fetal smallness affects 10% of pregnancies. Small fetuses are at a higher risk of adverse outcomes. Their management using estimated fetal weight and feto-maternal Doppler has a high sensitivity for adverse outcomes; however, more than 60% of fetuses are electively delivered at 37 to 38 weeks. On the other hand, classification using angiogenic factors seems to have a lower false-positive rate. Here, we present a protocol for the Fetal Growth Restriction at Term Managed by Angiogenic Factors Versus Feto-Maternal Doppler (GRAFD) trial, which compares the use of angiogenic factors and Doppler to manage small fetuses at term.

**Objective:**

The primary objective is to demonstrate that classification based on angiogenic factors is not inferior to estimated fetal weight and Doppler at detecting fetuses at risk of adverse perinatal outcomes.

**Methods:**

This is a multicenter, open-label, randomized controlled trial conducted in 20 hospitals across Spain. A total of 1030 singleton pregnancies with an estimated fetal weight ≤10th percentile at 36+0 to 37+6 weeks+days will be recruited and randomly allocated to either the control or the intervention group. In the control group, standard Doppler-based management will be used. In the intervention group, cases with a soluble fms-like tyrosine kinase to placental growth factor ratio ≥38 will be classified as having fetal growth restriction; otherwise, they will be classified as being small for gestational age. In both arms, the fetal growth restriction group will be delivered at ≥37 weeks and the small for gestational age group at ≥40 weeks. We will assess differences between the groups by calculating the relative risk, the absolute difference between incidences, and their 95% CIs.

**Results:**

Recruitment for this study started on September 28, 2020. The study results are expected to be published in peer-reviewed journals and disseminated at international conferences in early 2023.

**Conclusions:**

The angiogenic factor–based protocol may reduce the number of pregnancies classified as having fetal growth restriction without worsening perinatal outcomes. Moreover, reducing the number of unnecessary labor inductions would reduce costs and the risks derived from possible iatrogenic complications. Additionally, fewer inductions would lower the rate of early-term neonates, thus improving neonatal outcomes and potentially reducing long-term infant morbidities.

**Trial Registration:**

ClinicalTrials.gov NCT04502823; https://clinicaltrials.gov/ct2/show/NCT04502823

**International Registered Report Identifier (IRRID):**

DERR1-10.2196/37452

## Introduction

### Background

Fetal smallness affects around 10% of pregnancies [1]. Small fetuses are at a higher risk of intrauterine death and adverse perinatal outcomes [2]. In order to prevent these adverse outcomes, identification and appropriate management of small fetuses are crucial [3,4]. Based on gestational age (<32 weeks of gestation versus ≥32 weeks of gestation) at the time of disease onset, 2 distinct patterns of severity are observed in small fetuses, with the more severe cases being those with onset early in pregnancy (<32 weeks of gestation) [5]. In these cases, management is mainly based on fetal Doppler and indications for delivery are quite consistent [2], generally resulting in preterm neonates. However, most cases are diagnosed at a later gestational age (≥32 weeks) and, in this particular context, there is no clear consensus on the appropriate interventions to prevent adverse perinatal outcomes [6-8].

Moreover, the severity of fetal smallness is usually classified into 2 categories: fetal growth restriction (FGR), which is defined as a fetus failing to reach its genetically predetermined growth potential, and small for gestational age (SGA), which is defined as a fetus being small but without an increased risk of adverse perinatal outcomes. SGA fetuses are commonly referred to as constitutionally small fetuses [1,8]. Several criteria based on Doppler studies, growth velocity, and biometric percentiles are available to discriminate between SGA and FGR fetuses [2,8,9]. One of the most widely used classifications, as well as the one used in most maternity wards in Spain, is the one proposed by Figueras and Gratacós [8]. This classification, based on estimated fetal weight (EFW) and feto-maternal Doppler, allows the identification of the subset of small fetuses at a greater risk of perinatal complications (ie, true FGR fetuses) and the subset of small fetuses with a risk of perinatal complications similar to that of a normally growing fetus (ie, constitutionally small or SGA fetuses). According to several guidelines, FGR fetuses may benefit from early-term elective delivery (at 37-38 weeks), while SGA fetuses require closer monitoring, but not elective delivery until full term (39-40 weeks). FGR/SGA classification based on Doppler and EFW percentiles has a high sensitivity for adverse perinatal outcomes; nevertheless, more than 60% of fetuses with an EFW below the 10th percentile are classified as FGR and, therefore, will be delivered at 37 to 38 weeks [8]. Neonates delivered at 37+0 to 38+6 weeks+days of gestation are considered early-term and have poorer neonatal outcomes than full-term neonates (≥39 weeks of gestation) [10-12]. For this reason, early-term elective delivery should be restricted to FGR fetuses at an actual risk for adverse outcomes.

### Placental Insufficiency and SGA/FGR

The precise pathophysiology of SGA/FGR is unknown, but placental insufficiency is a common finding [13,14]. Several studies have reported histopathological findings related to placental malperfusion in SGA and FGR pregnancies [15,16]. The severity of the underlying placental insufficiency can be assessed by Doppler of the feto-maternal circulation [15,17]. Some studies have also shown an association between placental findings consistent with maternal vascular malperfusion and angiogenic imbalance involving a decrease of placental growth factor (PlGF), a proangiogenic factor, and an increase in soluble fms-like tyrosine kinase-1 (sFlt-1), an antiangiogenic factor, resulting in an increased sFlt-1/PlGF ratio [18-20].

### Management of SGA/FGR Pregnancies: EFW

As is widely known, there is an inversely proportional relationship between EFW and the risk of adverse perinatal outcomes [21-23]. For this reason, in DIGITAT (Disproportionate Intrauterine Growth Intervention Trial At Term), the only clinical trial ever conducted to evaluate the role of early-term elective delivery in improving perinatal outcomes of small fetuses, the only inclusion criterion was an EFW below the 10th percentile [24]. In that study, fetuses with an EFW below the 10th percentile were randomized into two groups: (1) early-term induction of labor and (2) expectant management until the onset of spontaneous labor. Perinatal outcomes were compared between the groups, showing that systematic early-term labor induction in pregnancies with small fetuses did not improve perinatal outcomes. By contrast, there was a significant increase in the number of admissions to the neonatal intensive care unit (NICU) and intermediate care unit for early-term neonates (51.1%) as compared to full-term neonates (39.8%). Since no differences were found in the baseline characteristics of the groups at enrollment, it is fair to assume that this 11.3% difference in neonatal admissions was mainly due to differences in gestational age at delivery between the groups. For this reason, a Cochrane review in 2015 [7] concluded that there is no evidence suggesting that early-term elective delivery of small fetuses (based only on EFW) should be recommended to avoid adverse perinatal outcomes. It must be noted that in DIGITAT, other factors predictive of poor prognosis in small fetuses, such as the amount of amniotic fluid, feto-maternal Doppler, or biophysical profile score, were not taken into account. Therefore, it might be possible that with more accurate identification of small fetuses who are actually at a higher risk of perinatal complications (ie, those with FGR), early-term elective delivery would have been found to improve perinatal outcomes as compared to the expectant management group.

### Management of SGA: Feto-Maternal Doppler

In recent years, and after the publication of DIGITAT, several studies have evaluated the role of feto-maternal circulation assessment by Doppler ultrasound in small fetuses [25-28]. These studies have shown that Doppler assessment allows identifying the subset of small fetuses at a higher risk of adverse perinatal outcomes (ie, those with FGR). Historically, umbilical artery (UA) pulsatility index (PI) assessed with Doppler has been considered the standard parameter to identify FGR. However, a large proportion of small fetuses with normal UA PI (ie, <95th percentile) have poorer perinatal outcomes than normally growing fetuses [21,29,30]. Thus, UA PI alone cannot be used to discriminate SGA from FGR fetuses [1,29]. Further studies showed that other Doppler parameters might have a greater predictive ability for adverse outcomes in late-onset SGA and FGR: cerebroplacental ratio (CPR), middle cerebral artery (MCA) PI, and uterine artery (UtA) PI [1,26,31,32]. According to these studies, abnormal CPR (ie, <5th percentile), MCA PI (ie, <5th percentile), or UtA PI (ie, >95th percentile) may be able to identify small fetuses at a higher risk of adverse outcomes (ie, FGR). A study including these criteria showed that small fetuses with abnormal Doppler parameters accounted for 60% of all small fetuses, indicating that more than half of fetuses with an EFW below the 10th percentile would be classified as FGR and that according to our current protocol, early-term induction of labor would therefore be recommended [25]. In the earlier study, induction of labor was recommended at 37 weeks of gestation in FGR fetuses (small fetuses with an EFW below the 3rd percentile or with an EFW below the 10th percentile accompanied by the presence of any abnormal Doppler parameter), while for other pregnancies with an EFW below the 10th percentile (ie, SGA fetuses) induction of labor was recommended at 40 weeks. Following that protocol, 134 cases (26.3%) had an adverse outcome, including, nonexclusively, 46 cases of neonatal acidosis and 106 cases of emergency cesarean delivery due to nonreassuring cardiotocography (CTG). Neonatal acidosis in that study was defined as a UA pH below 7.15 and a base excess greater than –12 mEq/L.

### Management of SGA: Angiogenic Factors

To date, few studies have evaluated the usefulness of angiogenic factors (AFs) in the management of late-onset or term SGA/FGR pregnancies. These studies show that the higher the sFlt-1/PlGF ratio, the worse the prognosis for small fetuses and the greater the risk of developing preeclampsia (PE), which in turn worsens maternal prognosis [19,33-35]. Recently, a large observational study compared the identification of term (36+0 to 37+6 weeks+days) small fetuses (EFW below the 10th percentile) at a higher risk of adverse outcomes using the standard Doppler assessment versus a new approach based on AFs [36]. In that study, 521 fetuses were identified as small, of which 102 had abnormal AF values (sFlt-1/PlGF ratio ≥38), whereas 412 had abnormal Doppler parameters. Therefore, according to the Doppler-based protocol, 79.1% (412/521) of small fetuses would have been classified as FGR, whereas according to the new AF-based approach, only 19.6% (102/521) of small fetuses would have been classified as FGR. By contrast, both approaches had a similar negative predictive value for adverse perinatal outcomes (99.3% and 99%, respectively), indicating a good, similar prognosis for those pregnancies not classified as FGR regardless of the classification used. Therefore, classification based on AFs seems more accurate and may have a lower rate of false positives than the Doppler-based protocol for the identification of small fetuses at a higher risk of adverse outcomes.

### Early-term Delivery: Short-term and Long-term Consequences

It might seem that whether a delivery is early term (<39 weeks) or full term (≥39 weeks) is not very relevant in terms of postnatal prognosis. However, several studies have found increased immediate postnatal morbidity (such as admission to the NICU due to a need for respiratory support) [10] and poorer long-term outcomes, such as the development of diabetes, obesity, and respiratory morbidity, in infants born early term as compared to full term [11,12]. Thus, a reduction in the number of elective early-term deliveries due to FGR overdiagnosis would certainly lead to improved short-term and long-term postnatal outcomes, ultimately resulting in healthier infants and adults.

### Rationale for the Study

The most common protocols used worldwide for the management of late-onset SGA/FGR are based on Doppler assessment, which recommends elective delivery at 37 weeks (or even earlier) in FGR pregnancies [25,37,38]. According to a classification based on Doppler parameters and EFW percentiles, up to 79.1% of small fetuses would be classified as FGR. By contrast, when using the AF-based approach (sFlt-1/PlGF ≥38), only 19.6% of small fetuses would be classified as FGR [36]. Additionally, both approaches seem to have a similar ability to identify small fetuses at risk (ie, those with FGR), which may benefit from an earlier elective delivery. Therefore, the AF-based protocol may potentially reduce by up to 75.2% (from 79.1% to 19.6%) the number of pregnancies classified as FGR (in which labor would be induced at 37 weeks) without worsening perinatal outcomes. Moreover, reducing the number of unnecessary labor inductions would not only improve patients’ perception of medical attention, but also would reduce the costs and risks derived from possible iatrogenic complications, which in turn would reduce the rate of cesarean deliveries. Additionally, fewer inductions would lower the rate of early-term neonates, thus improving neonatal outcomes and potentially reducing long-term infant metabolic, endocrine, and respiratory morbidities.

The sFlt-1/PlGF ratio has been shown to accurately predict PE and associated complications several weeks before onset [39-42]. Therefore, a management protocol based on AFs may potentially reduce the rate of PE and other maternal complications associated with PE, such as placental abruption or eclampsia.

### Objectives

#### Primary Objective

To determine whether the classification of small fetuses as FGR or SGA based on AFs is not inferior to the standard clinical approach (based on EFW and Doppler percentiles) for the identification of fetuses at a higher risk of adverse perinatal outcomes (neonatal acidosis and cesarean section due to nonreassuring CTG).

#### Secondary Objectives

To determine whether (1) the lower false-positive rate using AFs instead of Doppler to identify small fetuses as FGR results in a reduced number of elective deliveries before 38, 39, and 40 weeks, (2) a lower rate of early-term elective deliveries results in a reduced number of deliveries (elective and spontaneous) before 38, 39, and 40 weeks, (3) a lower rate of early-term elective deliveries results in a reduced number of cesarean deliveries, (4) a lower rate of early-term elective deliveries results in a reduced number of neonatal admissions to the NICU and a lower rate of adverse perinatal outcomes, (5) the AF-based approach reduces PE incidence in pregnancies with small fetuses, and (6) the AF-based classification reduces the incidence of placental-related complications.

### Trial Design

This is a multicenter, open-label, randomized clinical trial. The study design adheres to the SPIRIT (Standard Protocol Items: Recommendations for Interventional Trials) quality standard criteria for randomized trials [43]. A pragmatic approach will be adopted in order to evaluate the effectiveness of the intervention in real-life, routine practice conditions. Therefore, each participating site will use the fetal growth charts, Doppler reference values, and methods for cervical ripening and labor induction usually applied in their clinical practice.

The clinical trial was entered in the ClinicalTrials.org registry on August 6, 2020 (NCT04502823).

### Inclusion Criteria

Inclusion criteria at the time of enrollment are as follows: (1) age at least 16 years, (2) singleton pregnancy, (3) ultrasonographic EFW ≤10th percentile between 36+0 and 37+6 weeks+days of gestation, (4) sFlt-1/PlGF ratio measured between 36+0 and 37+6 weeks+days of gestation, (5) randomization between 36+0 and 37+6 weeks+days of gestation, and (6) gestational age confirmed by fetal crown-rump length measurement during the first trimester scan (from 11+0 to 13+6 weeks+days of gestation) or by in vitro fertilization dates.

### Exclusion Criteria

Exclusion criteria at the time of enrollment are as follows: (1) major fetal malformations or genetic disorders, (2) fetal death, (3) absent or reversed end-diastolic flow in UA Doppler, (4) nonreassuring CTG, (5) preeclampsia, (6) diminished fetal movements, (7) biophysical profile score ≤6, (8) oligohydramnios, and (9) refusal to give informed consent.

### Intervention

First, gestational age (by fetal crown-rump length measurement at 11+0 to 13+6 weeks+days) [44] and EFW ≤10th percentile will be confirmed [45-49]. After giving their written informed consent, trial participants will be randomized into 2 groups: intervention and control.

In the intervention group, the sFlt-1/PlGF ratio will be revealed to investigators so they can act according to the results. When the sFlt-1/PlGF ratio is ≥38, the fetus will be classified as FGR. The remaining cases will be classified as SGA. In the intervention group, the UA PI, MCA PI, CPR, and UtA PI percentiles will be concealed to obstetricians in order to avoid any influence that this information might have on their interpretation of fetal movements or CTG.

In the control group, the sFlt-1/PlGF ratio will be concealed to investigators and the standard Doppler-based approach will be used for fetal monitoring [1]. Thus, fetuses with an EFW <3rd percentile or ≤10th percentile accompanied by an abnormal feto-maternal Doppler (UA PI >95th percentile, MCA PI <5th percentile, CPR <5th percentile, UtA PI >95th percentile, or a combination of these markers) [50-53] will be classified as FGR. The remaining cases will be classified as SGA.

In both groups, when a fetus is classified as FGR, immediate (within 24 hours) elective delivery at ≥37 weeks of gestation will be recommended; when a fetus is classified as SGA, elective delivery will be delayed until 40 weeks of gestation. From randomization to delivery, all SGA pregnancies in both groups will receive weekly follow-ups consisting of fetal ultrasound (including fetal growth, amniotic fluid deepest vertical pocket, fetal movements, and feto-maternal Doppler), conventional CTG, and measurement of the sFlt-1/PlGF ratio (which will be concealed or revealed depending on the allocated group).

In both groups, if at any time after enrollment any of the following is present, immediate (within 24 hours) delivery will be recommended: UA with absent or reversed end-diastolic flow, nonreassuring CTG, PE, diminished fetal movements, biophysical profile score ≤6, or oligohydramnios (largest vertical pocket <2 cm). The flow chart in Figure 1 illustrates the management of participants from consent through follow-up.

**Figure 1 figure1:**
[figure not shown]
Flow chart of study intervention and management. AEDF: absent end-diastolic flow; CPR: cerebroplacental ratio; CTG: cardiotocography; EFW: estimated fetal weight; MCA: middle cerebral artery; PI: pulsatility index; PlGF: placental growth factor; REDF: reversed end-diastolic flow; sFlt-1: soluble fms-like tyrosine kinase-1; UA: umbilical artery.

According to recommendations of the National Institute for Health and Care Excellence (NICE) [54], labor will be induced in pregnancies with a Bishop score [55] ≤6 by promoting cervical ripening with vaginal administration of dinoprostone or misoprostol or with a cervical balloon, as per each site’s usual protocols (Table 1).

In pregnancies with a Bishop score >6, labor will be induced by amniotomy, intravenous oxytocin infusion, or both in all participating sites. Indications for elective cesarean delivery will be as follows: at least 2 previous cesarean deliveries, UA with absent or reversed end-diastolic flow, nonreassuring CTG, abnormal fetal presentation (breech or transverse lie position), placental abruption, PE with severe features requiring immediate delivery (pulmonary edema, serum creatinine >1.1 mg/dL, oliguria [≤500 ml in 24 h or <20 ml/h], persistent hypertension despite appropriate antihypertensive therapy, persistent cerebral or visual disturbances, or eclampsia), and participants refusing induction of labor. Other less frequent indications may occur and will be classified as “other.” Indications for intrapartum cesarean delivery will be as follows: prolonged labor, failed induction of labor, nonreassuring CTG, placental abruption, and PE with severe features requiring immediate delivery. Other less frequent indications may occur and will be classified as “other.”

Prolonged labor will be defined according to the NICE guidelines for intrapartum care of healthy women and babies [56]. According to these guidelines, a delay in the first stage of labor is suspected if cervical dilatation is <2 cm after 4 hours. After 2 hours, delay will be confirmed if progress is <1 cm, and oxytocin will be offered. Prolonged labor will be confirmed if dilatation has increased <2 cm after 4 hours of oxytocin infusion. The maximum duration of cervical ripening treatment will vary depending on the method, with 12 hours for the cervical balloon, 16 hours for misoprostol, and 24 hours for dinoprostone. Failed induction of labor will be defined as not entering the active phase of labor after cervical ripening along with 6 to 8 hours of oxytocin infusion.

**Table 1 table1:** Cervical ripening mechanisms used at each participating site. For labor induction, classification of fetuses as being small for gestational age or having fetal growth restriction will be based on the Doppler criteria, as in the control group [1]. Dinoprostone (Propess; Ferring Pharmaceuticals Ltd) was administered at a 10-mg dose with a vaginal delivery system. Misoprostol (Misofar; Exeltis Healthcare SL) was administered at a 25-µg dose with a vaginal tablet. Cervical balloons used a double-balloon catheter plus stylet (Cook Medical).

Hospital	Fetal growth restriction	Small for gestational age
Vall d’Hebron	Dinoprostone	Dinoprostone
Torrejón	Cervical balloon	Dinoprostone
Joan XXIII	Misoprostol	Misoprostol
Alicante	Dinoprostone	Dinoprostone
Arrixaca	Dinoprostone	Dinoprostone
Parc Taulí	Dinoprostone	Dinoprostone
Cabueñes	Dinoprostone	Dinoprostone
Germans Trias	Dinoprostone	Dinoprostone
Son Llàtzer	Dinoprostone	Dinoprostone
Lozano Blesa	Cervical balloon	Dinoprostone
Althaia	Dinoprostone	Dinoprostone
A Coruña	Dinoprostone	Dinoprostone
Elche	Cervical balloon	Dinoprostone
Valme	Cervical balloon	Cervical balloon
Hospital Terrassa	Dinoprostone	Misoprostol
Mutua Terrassa	Dinoprostone	Misoprostol
Getafe	Cervical balloon	Cervical balloon
Puerta del Mar	Cervical balloon	Misoprostol
Josep Trueta	Misoprostol	Misoprostol
Candelaria	Dinoprostone	Dinoprostone

### Predictive Variables

Predictive variables include maternal sFlt1 and PlGF plasma levels (pg/ml), fetal EFW, results of a Doppler assessment (UA PI, MCA PI, CPR, and UtA PI percentiles), amniotic fluid vertical pocket, fetal movement and biophysical profile score, and conventional CTG interpretation. PlGF and sFlt-1 levels will be measured using the automated Elecsys electrochemiluminescence immunoassay platform (Cobas Analyzers; Roche Diagnostics).

Nonreassuring CTG before and during labor will be defined as sinusoidal fetal heart rate tracing or absent fetal heart rate variability accompanied by recurrent late decelerations, recurrent variable decelerations, or bradycardia [57].

In all settings, EFW will be calculated using the Hadlock formula [49]. EFW percentiles will be calculated using the reference charts of each site’s protocol. Fetuses with an EFW ≤10th percentile will be classified as small [45-48]. Doppler assessments will be performed following the International Society of Ultrasound in Obstetrics and Gynecology Practice Guidelines [58]. All participating sites will use the same reference values for calculating UtA PI percentiles [51]. Doppler percentiles for UA PI, MCA PI, and CPR will be calculated according to gestational age using the charts of each site’s protocol (Table 2). Gestational age will be determined by fetal crown-rump length measurement at 11+0 to 13+6 weeks+days of gestation [44] or in vitro fertilization date.

**Table 2 table2:** Reference charts at each participating site.

Hospital	Estimated fetal weight percentile	Umbilical artery pulsatility index percentile	Middle cerebral artery pulsatility index percentile	Cerebroplacental ratio percentile
Vall d’Hebron	Mikolajczyk RT et al [47]	Ciobanu A et al [50]	Ciobanu A et al [50]	Ciobanu A et al [50]
Torrejón	Marsál K et al [48]	Arduini D and Rizzo G [52]	Baschat AA and Gembruch U [53]	Baschat AA and Gembruch U [53]
Joan XXIII	Hadlock FP et al [49]	Arduini D and Rizzo G [52]	Baschat AA and Gembruch U [53]	Baschat AA and Gembruch U [53]
Alicante	Mikolajczyk et al [47]	Ciobanu A et al [50]	Ciobanu A et al [50]	Ciobanu A et al [50]
Arrixaca	Figueras F et al [45]	Arduini D and Rizzo G [52]	Baschat AA and Gembruch U [53]	Baschat AA and Gembruch U [53]
Parc Taulí	Hadlock FP et al [49]	Arduini D and Rizzo G [52]	Baschat AA and Gembruch U [53]	Baschat AA and Gembruch U [53]
Cabueñes	Hadlock FP et al [49]	Arduini D and Rizzo G [52]	Baschat AA and Gembruch U [53]	Baschat AA and Gembruch U [53]
Germans Trias	Hadlock FP et al [49]	Arduini D and Rizzo G [52]	Baschat AA and Gembruch U [53]	Baschat AA and Gembruch U [53]
Son Llàtzer	Figueras F et al [45]	Arduini D and Rizzo G [52]	Baschat AA and Gembruch U [53]	Baschat AA and Gembruch U [53]
Lozano Blesa	Figueras F et al [45]	Arduini D and Rizzo G [52]	Baschat AA and Gembruch U [53]	Baschat AA and Gembruch U [53]
Althaia	Figueras F et al [45]	Arduini D and Rizzo G [52]	Baschat AA and Gembruch U [53]	Baschat AA and Gembruch U [53]
A Coruña	Figueras F et al [45]	Arduini D and Rizzo G [52]	Baschat AA and Gembruch U [53]	Baschat AA and Gembruch U [53]
Elche	Papageorghiou AT et al [46]	Ciobanu A et al [50]	Ciobanu A et al [50]	Ciobanu A et al [50]
Valme	Figueras F et al [45]	Arduini D and Rizzo G [52]	Baschat AA and Gembruch U [53]	Baschat AA and Gembruch U [53]
Hospital Terrassa	Figueras F et al [45]	Arduini D and Rizzo G [52]	Baschat AA and Gembruch U [53]	Baschat AA and Gembruch U [53]
Mutua Terrassa	Hadlock FP et al [49]	Arduini D and Rizzo G [52]	Baschat AA and Gembruch U [53]	Baschat AA and Gembruch U [53]
Getafe	Figueras F et al [45]	Arduini D and Rizzo G [52]	Baschat AA and Gembruch U [53]	Baschat AA and Gembruch U [53]
Puerta del Mar	Mikolajczyk et al [47]	Ciobanu A et al [50]	Ciobanu A et al [50]	Ciobanu A et al [50]
Josep Trueta	Mikolajczyk et al [47]	Ciobanu A et al [50]	Ciobanu A et al [50]	Ciobanu A et al [50]
Candelaria	Figueras F et al [45]	Arduini D and Rizzo G [52]	Baschat AA and Gembruch U [53]	Baschat AA and Gembruch U [53]

Amniotic fluid volume will be determined measuring the deepest vertical pocket and oligohydramnios will be considered when depth is <2 cm [59]. Depending on each site’s protocol, fetal movement will be assessed subjectively or based on biophysical profile score, as described by Manning [60]. PE will be defined as new-onset high blood pressure (systolic blood pressure ≥140 mm Hg or diastolic blood pressure ≥90 mm Hg), worsening of previous high blood pressure in addition to new-onset proteinuria (≥300 mg protein in a 24-hour urine collection, protein/creatinine ≥0.3, or a dipstick reading of 1+), worsening of previous proteinuria, or according to at least one of the following signs and symptoms: cerebral or visual symptoms, raised liver enzymes, low platelet count, renal insufficiency, and pulmonary edema. PE with severe features will be defined as either systolic blood pressure ≥160 mm Hg or diastolic blood pressure ≥110 mm Hg, or PE with any of the following signs and symptoms: cerebral or visual symptoms, raised liver enzymes, low platelet count, renal insufficiency, and pulmonary edema [61].

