#### Secondary Outcomes

Composite adverse perinatal outcome will be defined as the presence of at least one of the following: fetal death, Apgar score <7 at 5 minutes, UA pH <7.05, admission to the NICU or a transitional care unit within 48 hours, birthweight <2000 grams, maternal admission to the obstetric intensive care unit within 48 hours (before or after delivery), and PE.

Composite adverse neonatal outcomes will be defined as the presence of at least one of the following: respiratory distress syndrome (respiratory rate >60 or <30 breaths/min, grunting on expiration, chest indrawing, central cyanosis, apnea, or the need for surfactant therapy in the neonatal period) [62], transient tachypnea, required ventilatory support, grade III or IV intraventricular hemorrhage, neonatal sepsis, hypoglycemia, necrotizing enterocolitis, neonatal jaundice (treated with phototherapy), neonatal seizures, pneumonia, meningitis, and neonatal death.

Other secondary outcomes will include the following: rates of elective delivery before 38, 39, and 40 weeks of gestation; rates of deliveries (elective and spontaneous) before 38, 39, and 40 weeks of gestation; rate of birthweight <2500 grams; rate of UA pH <7.10; rate of elective cesarean delivery; rate of cesarean delivery due to failed labor induction; rate of emergency operative vaginal delivery; and rate of placental-related complications, such as placental abruption, pregnancy hypertension, severe PE, eclampsia, stroke, maternal death, and postpartum hemorrhage.

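### As punctuated, the preeclampsia (PE) definition is a list of alternatives, so new-onset hypertension alone counts as PE and cannot be told apart from pregnancy hypertension

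*Protocol article*

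**What the plan says.** The PE definition is in the protocol article under Predictive Variables. It is a single sentence with four items:

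1. It opens "PE will be defined as new-onset high blood pressure", with thresholds of 140 mm Hg systolic or 90 mm Hg diastolic, followed by a comma.
2. The next item is "worsening of previous high blood pressure in addition to new-onset proteinuria", with the proteinuria thresholds in parentheses.
3. The third and fourth items run "worsening of previous proteinuria, or according to at least one of the following signs and symptoms: cerebral or visual symptoms, raised liver enzymes", and the list of signs then continues.

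The sentence after it begins "PE with severe features will be defined as either systolic blood pressure ≥160 mm Hg or diastolic blood pressure ≥110 mm Hg, or PE with"; its second limb is completed by a list of signs that repeats the one just given.

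The terms are then used in several places:
- **Secondary Objectives:** objective 5 is the incidence of PE.
- **Secondary Outcomes:** the composite adverse perinatal outcome ends with "maternal admission to the obstetric intensive care unit within 48 hours (before or after delivery), and PE". The placental-related complications are given as "placental abruption, pregnancy hypertension, severe PE, eclampsia, stroke, maternal death, and postpartum hemorrhage". Pregnancy hypertension is not defined anywhere in the article.
- **Exclusion Criteria:** PE is criterion 5.
- **Intervention:** PE prompts a recommendation of delivery within 24 hours in both arms. PE with severe features requiring immediate delivery is a cesarean indication.

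**The concern.** The words that join hypertension to proteinuria are attached only to worsening of previous hypertension. Nothing joins new-onset hypertension to a second finding, and nothing says that proteinuria or a sign must be accompanied by a blood pressure criterion. Someone coding the outcome from the sentence would count isolated findings as PE. Someone applying a two-part concept would not.

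This matters for reporting because PE is the whole of secondary objective 5 and one component of a composite. Twenty sites apply the sentence, and outcome assessors are not masked (Randomization, Masking, and Data Collection). If sites resolve the wording differently, the PE rate is not one quantity. A separate rate of pregnancy hypertension would also have no clear content.

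**Working it through.** The article states no PE rate or figure to reproduce, so the check is one of logic.

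**Two readings.** N = new-onset hypertension, W = worsening of previous hypertension, P = new proteinuria, Q = worsening proteinuria, S = at least one listed sign.

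- Literal reading: N or (W and P) or Q or S.
- Two-part reading: (N or W) and (P or Q or S).

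**Combinations.** Blood pressure has three states (none, new, worsening), proteinuria three (none, new, worsening) and signs two (absent, present), so 3 × 3 × 2 = 18.

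| Blood pressure state | PE, literal | PE, two-part |
|---|---|---|
| New-onset hypertension (6 combinations) | 6 | 5 |
| Worsening hypertension (6) | 5 | 5 |
| Neither (6) | 4 | 0 |
| Total (18) | 15 | 10 |

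The readings differ in 15 − 10 = 5 combinations, all PE only under the literal reading:
- new-onset hypertension alone;
- worsening proteinuria alone;
- a sign alone;
- worsening proteinuria plus a sign, without hypertension;
- new proteinuria plus a sign, without hypertension.

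**Set against Secondary Outcomes.** Under the literal reading every woman with new-onset hypertension has PE, so new-onset pregnancy hypertension without PE is an empty category. Under the two-part reading it is not empty. Worsening hypertension alone is PE under neither reading, so the overlap is complete for new-onset hypertension only.

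**Severe features.** The first limb (160 mm Hg systolic or 110 mm Hg diastolic) does not mention PE; the second limb does.
- Under the literal reading, new-onset hypertension at that level is already PE, so the gap concerns women with previous hypertension.
- Under the two-part reading, the gap covers any woman at that level with no proteinuria and no sign.

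Adopting the two-part reading therefore does not by itself make severe PE a subset of PE.

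**Illustrative size.** Assume that 3–6% of women develop isolated hypertension and 2–4% have hypertension with a second criterion. These are assumptions, not figures from the article. Ratio of literal to two-part count = (isolated + two-criterion) / two-criterion.

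| Isolated | Two-criterion | Ratio |
|---|---|---|
| 3% | 4% | 7/4 = 1.75 |
| 3% | 2% | 5/2 = 2.5 |
| 6% | 4% | 10/4 = 2.5 |
| 6% | 2% | 8/2 = 4 |

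The counted rate would be 5–10% instead of 2–4%. Isolated proteinuria and isolated signs are left out of this illustration.

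**The case against.** The best reply is that the intended meaning is recoverable. Listing pregnancy hypertension apart from severe PE makes sense only if hypertension alone is not PE. The final item of the definition reads more naturally as an alternative to proteinuria than as a free-standing diagnosis. The sentence cites a source and condenses a full protocol, neither of which is at hand. This stands as an account of what was probably meant. It does not repair the sentence, since the reader must supply both an or and a grouping that are absent. It also leaves the severe-features sentence unresolved.

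The reply also limits what may be inferred:

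- **That a single reading of 140/90 makes PE.** The article gives thresholds for new-onset high blood pressure and does not say how many readings are needed.
- **That the error differs by arm.** More intervention women would be expected to stay pregnant longer: in the observational cohort cited in the Introduction, 419/521 (80.4%) were below the angiogenic cut-off, against 109/521 (20.9%) not classified as growth restricted by Doppler. But the weekly follow-up under Intervention names ultrasound, cardiotocography and the sFlt-1/PlGF ratio, with no blood pressure or laboratory check. Longer pregnancy also gives more time for true PE, which is part of the effect of the strategy. Differential misclassification is possible but not shown.
- **That placental-related complications must change.** If they are analysed as one combined rate and pregnancy hypertension counts in it, a woman with new hypertension contributes under either label.

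**Conclusion.** The definition is wrong as written and should be clarified. Read literally, it counts three kinds of isolated finding as PE, removes the distinction between PE and new-onset pregnancy hypertension, and allows severe PE without PE. This rests on the grammar of the sentence and its conflict with Secondary Outcomes, not on any rate.

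The consequences are confined to secondary outcomes: PE incidence, the composite adverse perinatal outcome and, depending on how they are analysed, placental-related complications. The primary outcome does not include PE, and no sample size or power figure changes.

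The size is unknown. The range of 1.75 to 4 depends wholly on the assumed rates. A reader might take fourfold inflation as the result, but that figure pairs the highest assumed rate of isolated hypertension with the lowest assumed two-criterion rate. Nor does the article show that the trial will in fact count isolated findings as PE. It shows only that its stated rule permits this.

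**What to change.** For outcome counting:

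- Restate the PE definition with explicit AND/OR grouping that matches the intended source definition and is consistent with Secondary Outcomes.
- Define pregnancy hypertension so that it does not overlap with PE.
- Make severe PE a subset of PE.
- Apply the same rule to both arms.

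The same terms appear in Exclusion Criteria, in the delivery recommendation and cesarean indications under Intervention, and in Predictive Variables and Secondary Outcomes. The investigators must reconcile these passages. Which clinical rule applies to eligibility and delivery is theirs to decide, and the outcome wording should not settle it by default.

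The cost is a few lines of text and a derived variable, if the needed data exist. Recruitment began in September 2020, and the article does not confirm that blood pressure and laboratory values are recorded for every woman, so some retrieval from clinical records may be needed. The other downside is that fewer PE events may be counted, which lowers precision for secondary objective 5.
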